### Interventions

2.8

The treatment plan of the trial is based on the traditional moxibustion in the clinical treatment of KOA, combined with the characteristics of Jade moxibustion instrument itself, considering the standardized requirements of the trial design.

According to the literature review, the following 5 acupoints are selected for each treatment.ST35, ST34, EX-LE4, SP10, and Ashi point (i.e., tender point around the knee joint) are all located in the knee region, and they are common acupoints in the global clinical research of treating KOA.^[28]^ In anatomy, Acupuncture point ST35 and EX-LE4 are located close to the thinnest part of the knee joint, so the thermal effect of moxibustion and Jade moxibustion can directly reach the articular cavity. According to the biomechanical study, most of the clinical diagnosis and treatment guidelines of KOA pay special attention to the muscle strength training of quadriceps femoris.^[29–32]^ The muscle strength of extensor and flexor groups of knee joint is closely related to the symptoms of KOA.^[33]^ SP10 and ST34 are near the area of vastus medialis obliquus and lateral great respectively, so they may directly improve the state of quadriceps femoris. Ashi point is the most painful point according to the actual situation of the subjects.

Subjects are allowed to take concomitant medication, but we will encourage them not to change their medications during the trial. At the same time, other therapies are not allowed, such as acupuncture, sodium hyaluronate injection.

The treatment process will be supervised throughout by the staff of the research team. The two groups of subjects will be treated separately by the rigorously trained treatment operator.

Jade moxibustion Group

The Jade Moxibustion group will use the HX001 temperature-controlled energy knee pads produced by Jiaxing Fuqiduo Thermal Bed Co., Ltd. Jade kneecap will be electrified and preheated for 3 minutes until the temperature rises to 46°C, press the jade in the kneecap against the knee which can be fixed on the knee of the subject. If the patients felt burning at the skin, the temperature will be adjusted.

Traditional moxibustion group

The traditional moxibustion group will use stick-on moxa cone produced by Nanyang Hanyi Moxibustion Co., Ltd. The stick-on moxa cone will be ignited after being attached to the acupoints. When the patients felt burning at the skin, the moxa cone will be removed and a new one would be attached and ignited again. A small pillow will be placed in the popliteal fossa and keep the knee slightly bent and stick moxa cone on the acupoints of the subjects.

Treatment of 2 groups will last for 20 minutes, 3 times a week and altogether 12 times in 4 weeks (every Tuesday, Thursday, and Saturday). If the subject is unable to receive treatment on time, he or she will be required to complete the treatment within that week. If any adverse event occurs, treatment will be suspended, and the investigator can decide whether to terminate the treatment.

## Outcomes

3

If the subject had a single knee joint pain, the outcome assessment will be evaluated for that knee. If both knees were affected and only one of them met the inclusion criteria, only the eligible knee will be evaluated. If both knees met the inclusion criteria, select the knee with more pain for evaluation.

### Primary outcome indicators

3.1

The primary outcome measure is the change in pain relative to baseline at the Western Ontario and McMaster Universities Osteoarthritis Index (WOMAC) in 4 weeks. The most painful knee joint for the subject will be recorded at the baseline, which will be the joint we measured throughout the trial. We will also measure WOMAC pain at week 2, 8, 12, and 24.

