**Methods/Design::**

This is a 2-parallel-group, randomized controlled trial. A total of 148 subjects with KOA (Kellgren–Lawrence grade II or III) will be recruited and randomized to receive Jade moxibustion treatment or a traditional moxibustion treatment in a 1:1 ratio. Jade moxibustion group: The affected knee of the subjects will be covered with jade kneepad. Traditional moxibustion group: Chosen the ST35, ST34, EX-LE4, SP10 and Ashi points at the affected knee. The subjects will receive treatment three times a week, altogether 12 times in 4 weeks. The main outcomes are WOMAC knee pain score, knee function score and SF-36 quality of life questionnaire changes at the 4th week. Secondary outcomes include WOMAC knee pain score and knee function score, overall clinical efficacy evaluation, medication, safety evaluation at the 2nd, 12th, and 24th week, and cytokines related to osteoarthritis in serum.

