### Secondary outcome indicators

3.2

The most important secondary outcome measurement is the improvement of WOMAC function in week 4. We will also assess the total score, function score and stiffness score of WOMAC at baseline, weeks 2, 8, 12, and 24. Visual analog scale pain score will be used to evaluate the arthritis pain of subjects at baseline, weeks 2,4, 8, 12, 24. SF-36 will be used to measure the quality of life of the subjects in the 4th, 12th, and 24th week. In addition, we will evaluate the efficacy of a 5-point scale in the fourth week (1 = very poor, 2 = poor, 3 = general, 4 = OK, 5 = very good.).

Any adverse event, whether related to treatment, requires the subject and investigator to report on each treatment or visit. Side effects include redness and blisters by Jade moxibustion and traditional moxibustion. Serious adverse events will be reported to the Ethics Committee. During the follow-up period (week 5 to week 24), we will call the subject weekly to find out about the adverse reactions and side effects that may occur during the week.

After 4 weeks of treatment, investigator will ask the subjects about the safety of the treatment: safe, fewer safe, have safety problem, and have serious safety problem. After each treatment we will ask the subject's feeling: “What do you feel during the treatment? 1. Heat; 2. Cold; 3. Pain; 4. no feeling; 5. Other, please describe”

The subjects will be allowed to take the analgesic or non-steroidal anti-inflammatory drugs used before the test, we will ask subjects to record the daily dose during the entire clinical trial, and then analyze the changes in the dose.

We will measure the outcome of the baseline, week 2, 4, 8, and 12 at the hospital. For the outcome of Week 24, we will mail the questionnaire to the subjects and ask them to post them back after filling them out.

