### Sample size

3.5

There is study indicates that at least a 36% increase in WOMAC score is considered effective.^[36]^ In the previous study of the research group, the average effective rate of the Jade moxibustion group was 55.56%, compared with 46.51% in the traditional moxibustion group. Based on the results of our pilot study and previous reports, we used non-inferiority test to calculate the sample size (α = 67 per group) with α = 0.025, 1−β = 80%, and a cutoff of 0.5. In other words, we expect a sample size of 62 subjects per group to be sufficient to detect statistically significant differences between the 2 groups. There were no cases of shedding in the 2 treatment groups in the previous trial. In order to prevent the occurrence of shedding resulting in insufficient sample size (preset 10% shedding rate), we will recruit 74 subjects for each group, and a total of 148 subjects need to be recruited.

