### Statistical analysis

3.6

Intention-to-treat analysis is the principle of this study, which includes all subjects in the designated treatment group, as well as subjects who have completed at least one course of treatment. The significant difference level is set to 0.05. The baseline characteristics of subjects will be summarized in both groups. For continuous results, the normal distribution of the data is labeled as the mean (standard deviation). For the main outcome, the remission rate of the fourth week will be calculated and χ^2^ test will be used to compare the Jade moxibustion group with the traditional moxibustion group. For secondary outcomes, unpaired scores including WOMAC pain, functional and stiffness scores, SF-36, expectation and reliability of treatment, and overall treatment outcome will be compared at all follow-up time points in both groups. T-test or Wilcoxon rank sum test will be used to compare continuous variables. We will use SPSS version 22 (IBM SPSS Statistics, NY) for statistical analysis.

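### The primary endpoint is stated inconsistently: the declared week-4 WOMAC pain change has no primary analysis, and the remission rate analysed as main is never defined

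*Protocol article*

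**What the plan says.** Five places in the protocol article bear on the primary endpoint.

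- **Abstract, Methods/Design:** "The main outcomes are WOMAC knee pain score, knee function score and SF-36 quality of life questionnaire changes at the 4th week".
- **Section 3.1:** "The primary outcome measure is the change in pain relative to baseline"; the instrument is WOMAC and the time point is 4 weeks.
- **Section 3.2:** "The most important secondary outcome measurement is the improvement of WOMAC function in week 4". SF-36 is listed in the same section, so it too is secondary.
- **Section 3.5:** the sample size starts from a cited finding that "at least a 36% increase in WOMAC score is considered effective". It then uses effective rates of 55.56% (Jade) and 46.51% (traditional) from the group's earlier study.
- **Section 3.6:** "For the main outcome, the remission rate of the fourth week will be calculated", with a chi-square comparison of the groups. The next sentence begins "For secondary outcomes, unpaired scores including WOMAC pain, functional and stiffness scores" and goes on to include SF-36.

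**The concern.** A confirmatory trial needs one primary endpoint, and its definition, sample size and main test must all refer to it. Here the endpoint that section 3.1 declares is handled in section 3.6 only among the secondary comparisons. The endpoint that section 3.6 treats as main does not appear in sections 3.1 to 3.3. A statistician following the text could not tell which result decides the trial. The week-4 remission rate could not be computed either, because no rule says who is in remission.

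These are conflicting positive statements, not details that an article would leave to a fuller document. An analysis plan written later could not conform to all of them at once.

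**Working it through.** **1. The sections side by side**

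| Place | Main outcome | How many | Scale | WOMAC pain | WOMAC function | SF-36 |
|---|---|---|---|---|---|---|
| Abstract | Pain, function, SF-36 at week 4 | 3 | Scores / changes | Main | Main | Main |
| 3.1 | Week-4 change in WOMAC pain | 1 | Continuous | Primary | – | – |
| 3.2 | – | – | – | – | Leading secondary | Secondary |
| 3.5 | Effective rate | 1 | Binary | Not named | Not named | Not named |
| 3.6 | Week-4 remission rate | 1 | Binary | Secondary | Secondary | Secondary |

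The entries differ in number (three against one), in scale (continuous against binary) and in rank (WOMAC pain is primary in 3.1 and secondary in 3.6).

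**2. Can the remission rate be computed from the text?**

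It would need a score, a direction, a threshold and a time point. Section 3.6 gives only the time point. The 36% threshold in section 3.5 refers to a WOMAC score without saying whether that is pain or total. It is called effective rather than remission, and section 3.6 never takes it up. It is also worded as an increase, which on a pain score reads as worsening. Section 3.5 does not expressly say that the 55.56% and 46.51% rates were obtained with this threshold.

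**3. Does the sample size show which endpoint was meant?**

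Inputs from section 3.5: rates 0.4651 and 0.5556, α = 0.025 (taken as one-sided), power 80%, a cutoff of 0.5 with no scale given, and two figures per group, 67 and 62.

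For a binary rate with margin Δ:

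n = [p₁(1−p₁) + p₂(1−p₂)] × (1.960 + 0.842)² / (p₂ − p₁ + Δ)²

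The variance sum is 0.2488 + 0.2469 = 0.4957, the squared factor is about 7.849, and the rate difference is 0.0905.

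- Δ = 0.5, the stated cutoff read as a rate difference: 0.4957 × 7.849 / 0.5905² = 11.2, so 12 per group. The plan's figures are not reproduced.
- Δ = 0.15, an assumption: 0.4957 × 7.849 / 0.2405² = 67.3, so 68 per group, close to 67.

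For a continuous outcome with a margin of 0.5 SD and no true difference, also an assumption: 2 × 7.849 / 0.5² = 62.8, so 63 per group, close to 62.

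The final 74 per group follows from 67 (67 × 1.10 = 73.7) and not from 62 (62 / 0.90 = 68.9).

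The two figures might come from a binary and a continuous calculation, but that is an inference from assumed margins. The calculation does not settle which endpoint was intended. It does show that the size cannot be verified until the endpoint is fixed. The failure to reproduce 67 or 62 from the stated inputs is a separate matter.

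**The case against.** The strongest defence is that there is one underlying variable. Section 3.1 would name the measure (WOMAC pain), section 3.6 would summarise it as a proportion of responders, and the secondary pain scores in 3.6 would be those at other visits. A responder endpoint is legitimate, and 3.5 and 3.6 at least agree on a binary scale. This shows that the text can be repaired, not that it is consistent. No sentence derives remission from WOMAC pain, 3.5 speaks of a WOMAC score without naming pain, and 3.6 compares the secondary scores at all follow-up time points.

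Four stronger readings are tempting, and the document does not support them.

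- **That the trial would count deteriorating patients as responders.** The direction of WOMAC is not printed. The 36% sentence reports a cited study, the word effective shows that benefit is meant, and no analysis adopts the rule. It is probably a slip for improvement.
- **That SF-36 has no baseline.** Section 3.2 lists weeks 4, 12 and 24 for it, but the visit schedule (Table 1) is not shown. The same section also says in general that outcomes are measured at baseline.
- **That the false-positive rate is about 14%.** The sum 1 − 0.95³ = 0.143 assumes three independent tests, any one of which wins. Section 3.6 specifies one main test, pain and function are subscales of one instrument, and the declared aim is non-inferiority.
- **That dichotomising makes 67 per group act like about 43.** This assumes a normal outcome and a plan sized on the continuous scale. Section 3.5 gives planning rates, so a binary analysis loses nothing against that plan.

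**Conclusion.** The inconsistency is wrong as written and must be reconciled. It rests on the document's own words, without outside knowledge or calculation: a continuous primary in 3.1, a binary main analysis in 3.6 with WOMAC pain demoted, sizing on a rate in 3.5, and three main outcomes in the abstract against one in 3.1. The consequence is definite: the declared primary has no primary analysis, and the analysed outcome has no definition.

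No numerical bias or error rate can be attached to this. The 36% wording is a lesser query within the point. Reading it as worsening rests on the ordinary meaning of a pain score, and it should be checked against its source. A reader might also infer that the sponsor intends to choose among endpoints after seeing the data. Nothing in the document shows that, and neither the registry record nor any analysis plan is at hand.

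**What to change.** Name one primary endpoint and use it in the abstract, 3.1, 3.5 and 3.6.

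**Least disruptive route, which fits 3.5 and 3.6.** Write the week-4 responder rate into 3.1 as the primary. Define it in full: which WOMAC score, percentage improvement from baseline, and the same threshold that produced the 55.56% and 46.51% rates. Use one term throughout in place of both effective and remission. Make the week-4 change in WOMAC pain the leading secondary outcome. If the WOMAC total is the chosen score, confirm that Table 1 schedules it at week 4, because the list of visits for it in 3.2 omits that week.

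**Alternative.** Keep 3.1 as it stands. Make the between-group mean difference in week-4 WOMAC pain change the primary analysis in 3.6, and restate margin and power in 3.5 on that scale. The document gives neither a margin nor a standard deviation in WOMAC pain points, so both would have to be supplied and justified.

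Under either route, list function and SF-36 as secondary in the abstract. After checking the cited source, correct the 36% sentence from increase to improvement (reduction).

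The cost is protocol wording and alignment of the registry entry. The alternative route adds a new margin and power statement, which could change the required number of subjects.

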### Study setting, recruitment, and ethics

2.2

Recruitment will be carried out in Tongren Hospital Affiliated to Shanghai Jiaotong University and Shanghai Pudong Hospital of Traditional Chinese Medicine. A total of 148 subjects with KOA will be enrolled. The study was approved by the medical ethics review committees of Tongren Hospital (No. Tongren 2019-022-02). Recruitment will be carried out through social platform, out-patient department, community propaganda and other ways. Investigator will contact people who are willing to participate in the study by telephone, conduct preliminary screening according to the inclusion and exclusion criteria, and then, if appropriate, arrange the acupuncture specialist for face-to-face baseline visit at an appropriate time, meanwhile the subjects will receive radiographic evaluation. The investigator will introduce the research protocol (i.e., the research purpose, procedures and time commitment and potential risks and benefits related to the research) in detail to potential subjects and obtain written informed consent. The subjects’ privacy information will be protected. Each subject will be given a unique random number as a direct identifier of the case report.

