### Inclusion criteria

2.3

1.Age 50 to 75 years old.2.According to the American College of Rheumatology Diagnostic Criteria for KOA.^[22–26]^3.Radiologic confirmation of KOA (Kallgren-Lawrence level ≥1).^[27]^4.Moderate or greater knee pain on most days of the past month; the subject's visual analog scale baseline score for arthritic pain is 40 points and above.5.Agreed to be randomly assigned, understand and would like to sign an informed consent.

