### Randomization

2.6

A total of 148 subjects with KOA who are eligible per protocol will be randomly assigned to group A - Jade moxibustion group or group B - traditional moxibustion group in a 1:1 ratio. The subject will first receive a brief phone consultation, after that, the subject will be allocated to the site. After the investigator and the subject signed the informed consent, the investigator will perform a simple rheumatic examination. The investigator will make a diagnosis based on the knee x-ray film brought by the subject or the knee X-ray performed at site. Only the subject who meet the inclusion/exclusion criteria will be randomized by central network randomization program. Then investigator will make baseline assessment and arrange treatment.

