### Stratification

2.7

The subjects will be stratified according to the number of lesions of the KOA (i.e., dual-joint and mono-articular).

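### Sections 3 and 3.1 can name different index knees, and the text leaves open whether the knee is fixed before or after the arm is known

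*Protocol article*

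**What the plan says.** **Which knee.** Section 3 (Outcomes) sets a rule by case. With one painful knee, that knee is assessed. With two affected knees of which one qualifies: "If both knees were affected and only one of them met the inclusion criteria, only the eligible knee will be evaluated". With two qualifying knees: "If both knees met the inclusion criteria, select the knee with more pain for evaluation". Section 3.1 (Primary outcome indicators) has a single rule: "The most painful knee joint for the subject will be recorded at the baseline, which will be the joint we measured throughout the trial". Eligibility does not appear in it.

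**When.** Section 2.6 (Randomization) runs through consent, examination and X-ray, and then says: "Only the subject who meet the inclusion/exclusion criteria will be randomized by central network randomization program". The next sentence reads: "Then investigator will make baseline assessment and arrange treatment". Two other places suggest a different order. Section 2.2 has the investigator "arrange the acupuncture specialist for face-to-face baseline visit at an appropriate time" during screening. Section 2.3 makes it an entry criterion that the subject's "visual analog scale baseline score for arthritic pain is 40 points and above".

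**Who knows the arm.** The Discussion (section 4) concedes that operators will know the allocation and that this may bias subjects. The article describes no blinding of subjects or outcome assessors.

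**The concern.** The primary outcome is the change in WOMAC pain from baseline to week 4 in one designated knee. That outcome is well defined only if everyone would pick the same knee for a given subject, and if the pick cannot depend on the arm.

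Both conditions are in doubt. A site following section 3.1 literally could score a knee that a site following section 3 would not. And if the knee is written down at a baseline assessment that follows randomisation, whoever records it may already know the arm. In a subject with two painful knees, the judgement of which hurts more could then be influenced by that knowledge. The baseline WOMAC, from which the change is calculated, would be exposed in the same way. A choice of knee made after allocation cannot be undone in the analysis.

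**Working it through.** The point rests on no figure in the plan, so the check compares the rules case by case and then sets out the order of events.

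**Step 1: the two knee rules.**

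| Configuration | Section 3 | Section 3.1 | Same knee? |
|---|---|---|---|
| One painful knee | that knee | that knee | yes |
| Both knees eligible | more painful | more painful | yes |
| Both affected, one eligible, eligible knee worse | eligible | most painful = eligible | yes |
| Both affected, one eligible, ineligible knee worse | eligible | most painful = ineligible | **no** |

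The rules conflict in one configuration of four. This counts configurations, not subjects, and the article gives no frequencies.

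**Step 2: how the fourth case can arise.** If the less painful knee meets the pain threshold in section 2.3, the more painful one will normally meet it too. It must therefore fail on something else. The clearest candidate is radiographic confirmation: section 2.3 asks for Kellgren–Lawrence grade 1 or higher, a low bar. The abstract speaks of grade II or III, which would make the case more frequent. That difference is a separate matter.

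**Step 3: the order of events.**

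- Section 2.6: eligibility check, then central randomisation, then baseline assessment. This is the only explicit sequence in the article.
- Section 2.2: the face-to-face baseline visit belongs to screening, together with the X-ray.
- Section 2.3: a baseline pain score decides entry, so it must exist before randomisation.
- Section 2.7: one versus two affected joints is the stratification factor, so the number of affected joints must also be known by then. Which knee is worse is not part of that factor.

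Some baseline information therefore precedes randomisation, and something called baseline assessment follows it. Section 3.1 records the knee at baseline without saying which of the two is meant. No sentence fixes the index knee before the arm is released.

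**Step 4: can the size be estimated?** For a choice of knee that depends on the arm, the shift in the between-arm response rate would be roughly

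shift = (share of subjects with two affected knees) × (share of those whose knee is chosen according to arm) × (difference in response between the two knees).

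The article supplies none of the three factors, so any number would be made up entirely of assumptions. None is given here.

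**The case against.** The strongest reply is that section 3 is the full rule for every outcome and section 3.1 only abbreviates it, adding that the knee stays the same throughout. On timing, eligibility is settled before randomisation and pain has already been scored for entry. When both knees qualify, the rule is deterministic, so steering by arm would mean overriding or repeating a score already on file. The trial is also nowhere called open-label, and a condensed article need not spell out every step.

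Much of this stands. The conflict is narrow, the order of events is inconsistent rather than plainly wrong, and influence on the choice of knee is confined to subjects with two affected knees. Two things remain. Section 3.1 does not refer back to section 3, and it is the more specific text for the primary outcome. The only explicit sequence puts baseline assessment after allocation. Both are statements in the article, not details left to a fuller document. As for masking, a heated kneepad and burning moxa cones are visibly different, so an unblinded trial is a fair inference, though not a stated fact.

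A reader might go further and infer that scoring the wrong knee dilutes a true deficit and so inflates the chance of a false non-inferiority claim. The documents do not support that. It would require the ineligible knee to show no difference between arms, yet the abstract has the affected knee treated, and nothing says that a painful but ineligible knee goes untreated or fails to respond. It would also require a share of mis-measured subjects, which is not given, and a margin on a known scale, whereas section 3.5 gives only a cutoff of 0.5 without naming the scale.

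**Conclusion.** The concern holds in a limited form. Sections 3 and 3.1 give different index knees when both knees are affected and the more painful one is ineligible; otherwise they agree. The timing of the baseline assessment is inconsistent between section 2.6 and sections 2.2 and 2.3. On the literal reading of section 2.6, the index knee in subjects with two affected knees, and the baseline WOMAC, could be set after the arm is known.

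This is a possible bias in the primary outcome, not a demonstrated one. The documents do not show that the knee is in fact chosen after allocation, nor that bilateral disease is common: its use for stratification shows only that both types of subject are expected. The size cannot be estimated from the article, and neither the sample size nor the stated error rates change because of this point. It is worth correcting because it concerns which joint supplies the primary outcome and because the correction is cheap.

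**What to change.** 1. In section 3.1, replace the sentence on the most painful knee with the rule of section 3: the index knee is the eligible knee; if both are eligible, it is the one with more pain at screening.
2. In section 2.6, state that the index knee and the baseline WOMAC are recorded before the arm is released, and that the knee is not changed afterwards. Use the term baseline in the same sense in sections 2.2, 2.3 and 2.6.
3. Enter the index knee in the central randomisation system as a required field.

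The cost is a sentence or two of wording, one extra field in the randomisation form, and the baseline assessment moved ahead of randomisation.
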